## 4. STUDY POPULATION

### 4.1 Population (base)

One-hundred thirty-two patients, above the age of 18, who are planned for surgical removal of a cholesteatoma using the CWU tympanomastoidectomy approach (with or without obliteration) between February 2025 and latest July 2026 in one of the participating centres will be asked to participate in this study. This includes all patients with an indication for a CWU tympanomastoidectomy, irrespective if this concerns a primary surgery or a revision surgery. We will not take into account gender, ethnic background or other characteristics of the study population as this has no influence on the disease or treatment. They must meet the following criteria to be eligible for the study.

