## SUMMARY

**Rationale:** The mainstay of cholesteatoma treatment is surgery with effective and safe removal of the disease as the principal goal. New techniques find their way in the international otologic community by proving lower recurrent and residual disease rates compared to the conventional techniques. One newly implemented and previously described technique is the obliteration technique of the mastoid. Although this approach has become more popular in recent years, high-quality evidence is missing.

**Objective:** The primary aim of this study is to investigate whether a canal wall up (CWU) tympanomastoidectomy with obliteration of the mastoid and paratympanic or epitympanic spaces reduces cholesteatoma recurrence and residual rates compared to the same approach without obliteration. Secondly, hearing outcomes after both surgical techniques are compared to investigate whether one of the two results in superior postoperative hearing. The quality of life will be measured using the Otology Questionnaire Amsterdam (OQUA). The economic evaluation will involve collecting the EQ-5D-5L, HUI-3, iPCQ and iMCQ questionnaires as well as direct intervention costs from the sponsoring centre.

**Study design:** The proposed study is a single-blind randomized controlled trial. One hundred seventy-eight patients will be included. Patients are randomized into one of two groups in an equal 1:1 allocation ratio. The randomization will be centre-stratified and a 4,6,8 block randomization will be used.

**Study population:** Patients above the age of 18 who undergo a CWU approach for removal of cholesteatoma in one of the participating centres.

**Intervention (if applicable):** Group A will undergo a CWU approach without obliteration and group B a CWU approach with obliteration.

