## 3. STUDY DESIGN

The proposed study design is a multicenter two-armed randomized controlled trial. It will be conducted using a single blind method. The patients will not know which surgical approach they received, which is necessary for the subjective measurement of the quality of life questionnaire. The surgeon will know which procedure he/she has performed as this is unavoidable. The surgeon will not write down which procedure the patient received in the surgical report or in the letter to the general practitioner. It will only be recorded in Castor and in the RFS map. De blinding (single-sided) will only be lifted if it is in the interest of the safety of the participant. De participant and/or general practitioner can request this from the treating physician (ENT-surgeon) who performed the surgery. The ENT-surgeon will decide if lifting of the blinding is necessary and inform the researcher about this event. In case of emergency and in absence of the treating physician, other medical specialists can lift the blinding by checking the placement of the patient in the RFS map. All medical specialists have access to the RFS map with information of the participants where an inclusion table with randomization is stored. This way it is possible to lift blinding 24 hours a day. After completion of the last quality of life questionnaire (at 36 months) the treatment group will also be added to the patient file in HiX. The patients are randomly assigned to one of the two groups (A or B). A web-based randomization tool in Castor will be used for the allocation and will be accessed by the researcher. The study will be conducted with a sufficient duration to gather the sample size needed. The setting is multi-center; both secondary and tertiary university hospitals will participate. The estimated duration of the study is 7 years (84 months): 1 year will be allocated for completing the inclusions and follow-up will be completed in the following 5 years. The last year will be used to analyze the data and round up the trial.

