#### 4.4 Sample size calculation

To detect a clinically relevant outcome of the primary objective (residual or recurrent disease) a sample size of at least 160 participants is needed. To calculate the sample size we used applicable and recent retrospective results of the UMC Utrecht (from January 2015 to March 2020) and reported recurrence rates from a systematic review of the literature, as this represents the most methodologically comparable and robust dataset currently available. We used our results to calculate the sample size needed with a power of 0.80. Relevant clinical difference was set at 20%. The calculation is based on a two independent proportions power analysis using a Z test with pooled variance with a alpha of 0.05 and a power of 0.80. Sample size calculations were performed with PASS 2008 and resulted in 80 patients per arm. To compensate for potential dropouts, a 10% margin is implemented, **resulting in 178 patients in total.**

| Two Independent Proportions (Null Case) Power Analysis                    |                               |                               |                                     |                                   |                     |                     |                 |                 |        |
|---------------------------------------------------------------------------|-------------------------------|-------------------------------|-------------------------------------|-----------------------------------|---------------------|---------------------|-----------------|-----------------|--------|
| Numeric Results of Tests Based on the Difference: P1 - P2                 |                               |                               |                                     |                                   |                     |                     |                 |                 |        |
| H0: P1-P2=0. H1: P1-P2=D1<>0. Test Statistic: Z test with pooled variance |                               |                               |                                     |                                   |                     |                     |                 |                 |        |
|                                                                           | Sample
Size
Grp 1
N1 | Sample
Size
Grp 2
N2 | Prop H1
Grp 1 or
Trtmnt
P1 | Prop
Grp 2 or
Control
P2 | Diff
if H0
D0 | Diff
if H1
D1 | Target
Alpha | Actual
Alpha | Beta   |

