## 6.2 Randomisation, blinding and treatment allocation

If they sign the informed consent form they will be randomly allocated to one of the two treatment groups (A or B) using the Randomization Tool in Castor. Patients will be randomly assigned to one of the two study groups (A or B). A website randomisation program built within Castor will be used for the randomization. After informed consent, patients will be randomized. This is a single blind study, meaning that only participants are blinded for the treatment allocation. The surgeons cannot be blinded, as they will know which procedure they performed. The surgeon will not write down which procedure the patient received in the surgical report or in the letter to the general practitioner. It will only be recorded in Castor and in the RFS map. De blinding (single-sided) will only be lifted if it is in the interest of the safety of the participant. De participant and/or general practitioner can request this from the treating physician (ENT-surgeon) who performed the surgery. The ENT-surgeon will decide if lifting of the blinding is necessary and inform the researcher about this event. Only in case of medical emergency and in absence of the treating physician, other medical specialists can lift the blinding by checking the placement of the patient in the RFS map. All medical specialists have access to the RFS map with information of the participants where an inclusion table with randomization is stored. This way it is possible to lift blinding 24 hours a day.

Stratification will be used to distribute the two groups as evenly as possible between the participating centres. Patients are randomized into one of two groups in an equal 1:1 allocation ratio. A 4,6,8 block randomization will be used.

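### Section 4.1 gives 132 patients where the Summary and Section 4.4 give 178; 132 cannot supply the number that the power calculation needs

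*Protocol*

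**What the plan says.** Section 4.1 (Population) opens with "One-hundred thirty-two patients, above the age of 18, who are planned for surgical removal of a cholesteatoma". It says that these patients, operated on between February 2025 and at latest July 2026 in the participating centres, will be asked to take part.

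The Summary (Study design) says "One hundred seventy-eight patients will be included".

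Section 4.4 says that "a sample size of at least 160 participants is needed", adds a 10% margin for dropout and ends with "resulting in 178 patients in total". The method is a "two independent proportions power analysis using a Z test with pooled variance with a alpha of 0.05 and a power of 0.80". The table of results shows 80 per arm, proportions 0.20 and 0.40, a two-sided alternative, power 0.8009 and actual alpha 0.0472.

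Section 6.5 relies on the 10% margin to keep power at 0.80 and says that withdrawn patients will not be replaced. Section 6.2 says "Patients are randomized into one of two groups in an equal 1:1 allocation ratio".

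On timing, Section 3 estimates 84 months in all: "1 year will be allocated for completing the inclusions", then five years of follow-up and a last year for analysis and closing the trial.

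**The concern.** The current text holds two incompatible patient numbers. Nothing marks 132 as a subset, a figure for one country or a count of evaluable patients.

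Centres, monitors and the ethics committee all use this number, and the claimed power depends on it. Withdrawn patients are not replaced, and Section 8.3 plans no interim analysis, so the protocol has no built-in step that would pick up a shortfall. The version footer is dated 25 March 2026, about four months before the latest surgery date in Section 4.1. The ambiguity therefore bears on when recruitment should end.

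**Working it through.** **Inputs.** Section 4.4: proportions 0.20 and 0.40, two-sided alpha 0.05, pooled-variance z test, 80 per arm, 10% margin. Section 6.2: 1:1 allocation. Section 4.1: 132 patients, so 132/2 = 66 per arm.

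**Step 1: reproduce the protocol's figures.** With x and y events in arms of size n and pooled proportion p = (x + y)/(2n), the statistic is

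z = (x/n − y/n) / √[p(1 − p)(2/n)],

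and the test rejects if |z| ≥ 1.96. Exact power is the sum, over all pairs (x, y) that reject, of Bin(x; n, 0.20) × Bin(y; n, 0.40). At n = 80 this gives 0.8009. The same sum with 0.40 in both arms gives 0.0472. Both agree with the table in Section 4.4 to four decimals. For dropout, 160/(1 − 0.10) = 177.8, which rounds up to 178. Section 4.4 is consistent in itself.

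**Step 2: compare 132 with the requirement.**

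- Against the number to be included: 178 − 132 = 46 too few.
- Against the evaluable minimum: 160 − 132 = 28 too few, before any loss.
- If 132 is the number approached, as Section 4.1 literally says, it still cannot yield 178, and every refusal widens the gap.

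**Step 3: power if recruitment stopped at 132.** With 10% loss, 132 × 0.9 = 118.8 patients remain, about 59 per arm. The cross-check is the normal approximation

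power ≈ Φ{[0.20√n − 1.96√(2 × 0.30 × 0.70)] / √(0.20 × 0.80 + 0.40 × 0.60)}.

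At n = 66 this is Φ[(1.625 − 1.270)/0.632] = Φ(0.561) = 0.712.

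| Randomised | Loss | Analysed per arm | Exact power | Normal approximation |
|---|---|---|---|---|
| 178 | none | 89 | 0.837 | 0.835 |
| 178 | 10% | 80 | 0.801 | 0.794 |
| 132 | none | 66 | 0.716 | 0.712 |
| 132 | 10% | 59 | 0.674 | 0.663 |

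**Step 4: the recruitment window (side note).** February 2025 to July 2026 inclusive is up to 18 months. Section 3 gives 12 + 60 + 12 = 84 months. Using the full window gives 18 + 60 + 12 = 90 months.

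**The case against.** The case for treating this lightly is that the governing number is clear. The figure 178 appears twice, rests on a calculation that reproduces, and underlies Section 6.5. Section 3 adds that the study will last long enough to reach the required sample. The figure 132 occurs once, in a sentence describing the population, and is neither a stopping rule nor an explicit target. Allocation runs centrally through one web tool, so no single centre would act on an all-centres total.

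Much of this stands, and it limits what may be concluded:

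- A reader might infer that the sample size calculation is wrong or that the trial has only 67% to 72% power. The protocol does not support that. Section 4.4 claims 0.80 for 80 per arm, which is correct, and it makes no power claim for 132. The fault is an inconsistency between sections, not an arithmetic error.
- A reader might infer that recruitment will close at 132. No passage instructs it.
- A reader might take 0.67 as the power at 132. That figure treats a tenth of the patients as contributing nothing, whereas Sections 8.1 and 8.2 plan multiple imputation and analysis by intention to treat. It is the complete-case figure, and 0.72 is the figure without loss.
- A reader might take 132 as left over from an earlier design. That is plausible, but the document does not show it.
- A reader might treat the timing as an equally firm contradiction. It is softer: July 2026 is an outer limit and 84 months is an estimate. The 90-month total assumes that the whole window is used.

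The objection does not remove the contradiction. Current text gives two sample sizes, and only one of them supports the stated power.

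**Conclusion.** The point holds as an internal inconsistency. The 132 in Section 4.1 contradicts the 178 in the Summary and Section 4.4, and no reading of it meets the requirement. The supported figure is 178.

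The statistical consequence is conditional. If recruitment stopped at 132, power would fall from 0.80 to about 0.72 with no loss, or about 0.67 with 10% loss. These values assume the protocol's own inputs: 20% against 40%, a two-sided pooled z test at 0.05, and equal arms. The mismatch in the recruitment window is a side note.

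**What to change.** Change Section 4.1 to 178 randomised patients, in line with the Summary and Section 4.4. Word it as the number randomised, not the number asked, since more will have to be approached if any decline. This is a one-line correction that changes neither the design nor the calculation.

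Only if 132 is the number the sponsor really intends to enrol, amend the Summary and Section 4.4 to match and restate the power as about 0.67 to 0.72 depending on loss.

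In the same amendment, state one recruitment window in Sections 3 and 4.1 and derive the total duration from it. This takes slightly more work, because two sections and the 84-month estimate may change.

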### 4.3 Exclusion criteria

A potential subject who meets any of the following criteria will be excluded from participation in this study:

- Cases of revision surgery due to residual disease with a normal, intact or reconstructed tympanic membrane
- Cases where a previous obliteration has taken place
- Cases of congenital cholesteatoma
- Patient with an indication for the surgery due to a disease other than cholesteatoma (chronic otitis media)
- In rare cases patients may have a pathology which makes obliteration unavoidable due to the invasiveness of the disease (e.g. cholesteatoma extension into and near

total destruction of the bony ear canal or bony tegmen plate). This is judged by the treating physician. These patients cannot be included because randomisation is not a possibility in these cases.

- Severe comorbidity with an expected survival of less than five years
- Comorbidity or disorder which could interfere with the completion of questionnaires (e.g. known psychiatric disorder, mental retardation)
- Compromising anatomical situation (i.e. radical cavity, Congenital craniofacial anomalies with involvement of the temporal bone and including cleft palate)
- Contraindication to undergo a diffusion-weighted magnetic resonance imaging (DW-MRI) (e.g. claustrophobic, metal parts of implants in the body such as a pacemaker)

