## 6. METHODS

### 6.1 Study parameters/endpoints

#### 6.1.1 Main study parameter/endpoint

The main endpoint is the number of patients with recurrent or residual cholesteatoma. Follow-up for recurrent/residual cholesteatoma will be performed after 6-18 weeks and after approximately 1, 3 and 5 years. Follow-up is done by micro-otoscopy and DW-MRI scans (after 1, 3 and 5 years) (see figure 1 for the follow-up steps). A newly formed retraction pocket from the tympanic membrane correlates with recurrent disease (clinical diagnosis), whereas cholesteatoma formation behind a normal or an intact tympanic membrane after primary surgery correlates with residual disease (radiologic diagnosis).

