#### 6.1.2 Secondary study parameters/endpoints

- **Baseline characteristics:**
  - Patient demographics (age (as collected by birthyear), gender), date of first presentation at the outpatient clinic, date of surgery, operated side (right/left), applied antibiotic treatment within in 2 weeks prior to surgery.
  - Co-morbidities and lifestyle factors: smoking, obesity, asthma, diabetes, COPD, allergies, rhinosinusitis.
  - Amount and type of all previous ear surgeries which are not mentioned in the exclusion criteria.
- **Hearing outcome:**
  - As measured by audiometric testing (pure-tone average thresholds (PTA) as calculated over 0.5, 1, 2 and 4 kHz for the air-conduction (AC) and bone-conduction (BC) and speech audiometry. This will be measured before the surgery, and at 6-18 weeks and around 1 year after surgery. The pre-operative audiogram should not have been measured more than 6 months prior to surgery.

- **Surgical characteristics:**

- A short 'standard' surgical report/template written by the participating otologists per center will be collected and used in the scientific publication to demonstrate any potential differences in surgical technique. This **does not** include patient information.
- STAMCO-classification: Localization and extension of the cholesteatoma, presence of preoperative complication status and the ossicular chain status before/at the time of removal of the cholesteatoma will be recorded. Any differences in outcomes in STAMCO classifications between the two randomized groups will be evaluated and described.

**Figure 2:** Localization, disease extension and complications as described by the STAMCO classification (18, ten Tije et al.)

[figure not shown]

- Material used for obliteration (Bonalive®, bonedust, hydroxyapatite, cartilage, muscle) as registered in the surgical report.

- Ossicular chain reconstruction (OCR); performed (yes/no), if yes, the used material and type of reconstruction (PORP, TORP, use of incus interposition, type 3 tympanoplasty) will also be reported.
- Surgical personnel: It is registered if an ENT-doctor in training (resident) or fellow has operated along with the specialist.
- Surgical time: Surgery time is recorded in minutes for each surgery and described.
- Revision surgery during follow-up: the information and observations as gathered by the surgical report will be collected from all revision surgeries performed during the follow-up of this study.
- **Complications**

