### **8.1 Primary study parameter(s)**

The data of our primary outcome are quantitative and will be presented as frequencies and proportions. To compare the difference in recidivism (recurrent and residual disease) at 12, 36 and 60 months between both surgical groups the Chi-squared test or Fisher's exact test will be used. The relative risk (RR) and absolute risk difference (RD) will be calculated as effect sizes using a generalized linear model for binomial outcome with a log-link (for RR) and identity link (RD). The primary analysis will be adjusted for site by including centre as covariate in a logistic regression model with treatment arm as the main predictor. All effect sizes will be accompanied by 95% confidence intervals. To graphically demonstrate the rates of recidivism, recurrent and residual disease over the follow-up time, a Kaplan-Meier analysis will also be performed and survival curves will be constructed. Multiple imputation will be used to deal with missing

outcomes. A 20% difference is defined as the threshold for clinical relevance and will be consistently applied in both clinical effectiveness analyses and the health economic evaluation.

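### Primary and revision operations are enrolled together, but the primary model omits revision status and the residual-disease wording does not clearly cover revision patients: a small precision gain and a definition to tidy, not a bias

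*Protocol*

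**What the plan says.** Protocol section 4.1 enrols all patients with an indication for canal wall up surgery, "irrespective if this concerns a primary surgery or a revision surgery". Section 4.3 narrows the revision group by two exclusions: "Cases of revision surgery due to residual disease with a normal, intact or reconstructed tympanic membrane" and "Cases where a previous obliteration has taken place". Other revision cases remain eligible.

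Section 4.1 adds that the trial will not take account of gender, ethnic background "or other characteristics of the study population as this has no influence on the disease or treatment".

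Randomisation is 1:1 in blocks of 4, 6 and 8, stratified by centre (Summary and section 6.2). The primary analysis in section 8.1 is "adjusted for site by including centre as covariate in a logistic regression model with treatment arm as the main predictor". Section 8.1 also reports a relative risk and a risk difference from log-link and identity-link binomial models, for which it names no covariates. Section 6.1.2 lists among the baseline data "Amount and type of all previous ear surgeries which are not mentioned in the exclusion criteria". In section 8 these baseline data are only described.

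Section 6.1.1 says that "cholesteatoma formation behind a normal or an intact tympanic membrane after primary surgery correlates with residual disease". The matching sentence on recurrent disease, which refers to a newly formed retraction pocket, carries no such limit. The main endpoint is the composite of recurrent or residual disease.

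**The concern.** Two separate matters arise from the mixed population.

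**Precision.** An ear that has already failed surgery may have a different risk of recidivism from one operated on for the first time. If so, a chance imbalance in revision cases shifts the observed effect, and leaving the factor out of the model forgoes some power. The variable needed is already collected. Because section 8.1 names the primary model and its covariate, a statistical analysis plan that added revision status would have to be reconciled with it.

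**Definition.** Section 4.1 uses primary surgery as the opposite of revision surgery. If section 6.1.1 is read with that meaning, disease behind an intact membrane after a revision trial operation is neither recurrent nor residual. The Summary and section 3 require a type to be determined for confirmed disease, and section 8.1 plans separate recurrent and residual curves, so centres could label such cases differently.

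**Working it through.** **The plan's own figure.** Section 4.4 gives 80 per arm for 0.20 v 0.40, two-sided alpha 0.05, pooled Z test, with power 0.8009 and actual alpha 0.0472. Exact binomial enumeration of that test at 80 per arm returns power 0.8009 and, with both rates at 0.40, alpha 0.0472. Allowing for 10% dropout, 160/0.9 = 177.8, so 178 in total or 89 per arm. The baseline figures reproduce.

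**Inputs not in the protocol (assumptions).** Revision share r = 20%, 30% or 40%. Odds ratio (OR) for recidivism, revision v primary, 1.5 to 4. Marginal risks are held at the protocol's 0.40 and 0.20.

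**Step 1: chance imbalance.** With 89 per arm and no balancing on revision status, the SD of the between-arm difference in revision share is sqrt(2r(1-r)/89).

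| r | SD | P(gap of 10 points or more) |
|---|---|---|
| 0.2 | 6.0 points | 0.095 |
| 0.3 | 6.9 points | 0.145 |
| 0.4 | 7.3 points | 0.173 |

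**Step 2: effect on the risk difference.** For each r and OR, solve (1-r)q + r·OR·q/(1-q+OR·q) = marginal risk for the primary-surgery risk q in each arm. The shift from a 10-point imbalance is 0.10 × the average, over the two arms, of the revision-minus-primary risk gap.

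| OR | Control-arm gap, r = 0.3 | Obliteration-arm gap, r = 0.3 | Shift, r = 0.3 | Shift, r = 0.2 to 0.4 |
|---|---|---|---|---|
| 1.5 | 9.8 points | 6.8 points | 0.8 points | 0.8 points |
| 2 | 16.8 points | 11.8 points | 1.4 points | 1.4-1.5 points |
| 3 | 26.5 points | 19.0 points | 2.3 points | 2.2-2.4 points |
| 4 | 33.2 points | 24.1 points | 2.9 points | 2.7-3.0 points |

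For scale, the standard error of the risk difference at 80 per arm is sqrt(0.24/80 + 0.16/80) = 7.1 points. A shift of 3 points is 3/7.1 = 0.42 of one standard error.

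**Step 3: power and type I error at 80 per arm.** Two simulations compare analyses without and with revision status.

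- Pooled Z test v Cochran-Mantel-Haenszel test stratified on revision status, 40,000 runs per scenario. At r = 0.3: OR 1.5, 0.802 v 0.798; OR 2, 0.799 v 0.801; OR 3, 0.799 v 0.816. Over r = 0.2 to 0.4, type I error of the unadjusted test lies between 0.046 and 0.049.
- Logistic model without v with revision status, 3,000 runs per scenario. At r = 0.3: OR 2, 0.799 v 0.806; OR 3, 0.784 v 0.809; OR 4, 0.806 v 0.835. At r = 0.4: OR 2, 0.797 v 0.799; OR 3, 0.806 v 0.830; OR 4, 0.800 v 0.833.

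The gain is therefore nil at OR 1.5 (about -0.4 points at r = 0.3), 0-1 point at OR 2, and about 2-3 points at OR 3-4.

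**Step 4: the definition.** Three places have to be read together. Section 4.1 contrasts primary with revision surgery and admits both. Section 6.1.1 attaches the residual category to primary surgery. The Summary and section 3 have the type of recidivism determined and recorded at the later revision operation, with no limit to first-time cases. Taken with section 4.1's meaning, section 6.1.1 leaves a gap for revision patients that the other two places do not. The composite counts confirmed disease of either type, so only the split is affected.

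**The case against.** The case for leaving the plan alone is substantial.

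- **No evidence of strength.** A reader might infer that revision status is a strong prognostic factor. The protocol gives no recidivism rate by primary or revision status and no revision share, and section 4.3 removes two revision subgroups. Plausible is as far as the document goes.
- **Chance imbalance is not bias.** A reader might infer that the primary estimate is biased. Randomisation makes any imbalance random, and the confidence interval already covers it. This stands.
- **No contradiction with the Introduction.** Section 1 lists patient-related factors and differing inclusion criteria as confounders. A reader might set this against the remark in section 4.1 about "other characteristics of the study population as this has no influence on the disease or treatment". But section 1 speaks of retrospective comparisons, a problem that randomisation addresses, and the remark leads into the eligibility criteria. Nor does excluding some revision cases contradict admitting others. What remains is that the remark gives its reason too broadly.
- **Choice of covariates.** Centre is the stratification factor, and adjusting for it is defensible. Further covariates may be left to an analysis plan that is not shown. That makes this a recommendation, not an error, though the two documents must agree.
- **The definition.** Primary surgery in section 6.1.1 may simply mean the trial operation, and the sentence is descriptive. A reader might infer that revision patients drop out of the main endpoint. They do not, because the composite counts them under either label. The ambiguity in the split remains.

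**Conclusion.** The point holds as a modest one. The population is mixed, the named primary model adjusts for centre only, and a usable baseline variable goes unused. On assumed revision shares of 20-40% and odds ratios of 1.5-4, a 10-point imbalance, expected in about 10-17% of such trials, moves the risk difference by about 1-3 points against the 20-point threshold. Adjustment is worth about 0-3 points of power. If the true odds ratio is near 1.5, there is nothing to gain.

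The definition issue does not depend on those assumptions. It is a wording ambiguity that affects how events are divided between recurrent and residual disease, and the curves drawn from that division.

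**What to change.** **Section 8.1.** Prespecify primary versus revision cholesteatoma surgery as a covariate beside centre in the logistic model. Define the derivation: the recorded variable covers any previous ear surgery, so the plan must say which entries count as revision for cholesteatoma. Use the same adjustment for the reported relative risk and risk difference; otherwise the effect sizes remain unadjusted. If the log-link or identity-link model fails to converge, obtain both measures by standardisation from the logistic model, and state this fallback in advance.

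**Section 6.1.1.** Refer to the index (study) operation instead of primary surgery, so that the recurrent and residual categories apply alike to all enrolled patients.

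**Section 4.1.** Limit the no-influence remark to saying that these characteristics do not restrict eligibility.

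**Cost.** Wording in three sections, a derivation rule, one model degree of freedom, and the possible convergence problem noted above. Randomisation, recruitment and data collection do not change. The covariate should be fixed before outcomes are known, and the definition before events are classified.
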